## Abstract

**Background:**

The mental and financial strain linked to unpaid caregiving has been amplified during the COVID-19 pandemic. In sub-Saharan Africa, carers of adolescents living with HIV (ALHIV) are critical for maintenance of optimum HIV treatment outcomes. However, the ability of caregivers to provide quality care to ALHIV is undermined by their ability to maintain their own wellbeing due to multiple factors (viz. poverty, stigma, lack of access to social support services) which have been exacerbated by the COVID-19 pandemic. Economic incentives, such as cash incentives combined with SMS reminders, have been shown to improve wellbeing. However, there is a lack of preliminary evidence on the potential of economic incentives to promote caregiver wellbeing in this setting, particularly in the context of a pandemic. This protocol outlines the design of a parallel-group pilot randomised trial comparing the feasibility and preliminary effectiveness of an economic incentive package versus a control for improving caregiver wellbeing.

**Methods:**

Caregivers of ALHIV will be recruited from public-sector HIV clinics in the south of the eThekwini municipality, KwaZulu-Natal, South Africa. Participants will be randomly assigned to one of the following groups: (i) the intervention group (*n* = 50) will receive three cash payments (of ZAR 350, approximately 23 USD), coupled with a positive wellbeing message over a 3-month period; (ii) the control group (*n* = 50) will receive a standard message encouraging linkage to health services. Participants will be interviewed at baseline and at endline (12 weeks) to collect socio-demographic, food insecurity, health status, mental health (stigma, depressive symptoms) and wellbeing data. The primary outcome measure, caregiver wellbeing, will be measured using the CarerQoL instrument. A qualitative study will be conducted alongside the main trial to understand participant views on participation in the trial and their feedback on study activities.

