Nudges are a key behavioural economics strategy (“nudge”) for health-related behaviour change [40, 41]. Nudges seek to influence decision-making by specifically targeting behavioural barriers. Nudges have been successfully used to develop low-cost solutions targeting key behavioural barriers and social norms impacting health outcomes [42]. Whilst there are mixed results on the effectiveness of nudges in certain settings, nudges have shown positive results in areas such as mental health [43, 44], HIV [45–47] and dietary choices [48]. In SSA, short-text messaging service (SMS) technology has been used in nudge approaches to deliver health information, motivate individuals to access care and adhere to treatment [47]. These studies also suggest that nudges can be readily brought to scale in these settings. Evidence from SSA indicates that SMS reminders sent to caregivers have been effective in promoting appointment attendance and medical adherence [47]. Key debates regarding the nudge approach revolve around its inability to solve complex health problems given its focus on targeting specific behavioural barriers when it comes to uptake, adherence and access to health interventions [49], the lack of causal evidence and lack of understanding of patterns [50, 51]. Ethical concerns noted about nudging are that it diminishes one’s autonomy and agency [51]. To our knowledge, no study has re-designed and evaluated these economic incentives, cash and SMS reminders, for the promotion of quality of life among caregivers of ALHIV.

Pilot and feasibility studies are an important first step in adapting and testing complex interventions in public health [52]. Pilot studies facilitate in-depth understanding of the conduct and applicability of an intervention which can enhance the design and conduct when evaluated at scale [53]. The overall aim of this pilot randomised control trial (RCT) is to evaluate the feasibility of a future large scale randomised controlled trial in examining the effectiveness of an economic incentive package (cash + SMS) in improving wellbeing among caregivers of ALHIV.

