#### Primary clinical outcome measures informing our sample size

Percentage change in wellbeing scores pre-vs. post-intervention:*Wellbeing* will be measured using the Care-related Quality of Life (CarerQol) instrument. The CarerQol instrument is a preference-based measure that was developed for use in economic evaluations [64], and has exhibited moderate construct validity (correlation co-efficient with CarerQol and self-rated burden dimensions ranging from 0.2 to 0.4) among older carers in the Netherlands [65]. Clinical and convergent validity have also been supported [66].Successful consent rate: a minimum of ≥ 80% of eligible participants enrolled in the studySuccessful retention rate: a retention rate of ≥ 80% of recruited participants

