### Blinding

This is an open label trial as field staff will be involved in the intervention delivery and study assessments. The statistician involved in the randomisation will be blinded to study arm. Participants will be encouraged not to disclose details regarding their wellbeing programme to other participants during the trial. We will at multiple points (consent, baseline interview, cash send, follow-up) encourage participants not to share their study details, including randomisation, to anyone else.

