### Sample size

Our primary outcome is pre-post between difference in caregiver wellbeing scores. Assuming a mean caregiver wellbeing VAS score of 6.5 in M1 versus 8.5 in M5 (SD1.9) in the intervention arm, we would need a minimum sample size of *n* = 15 per arm to have 80% power to detect a treatment effect of between δ = 0.6–0.5 [66, 70]. Thus a sample size of *N* = 100 will satisfy this primary outcome and give us enough sample to look at feasibility measures (consent and retention rate ≥ 80%), assuming *n* = 20 refuse to participate or are lost to follow-up.

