### Progression criteria

The following criteria must be met in order to consider progression to a main RCT:A retention rate of ≥ 80% of recruited participantsA minimum of ≥ 80% of eligible participants enrolled in the study

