## Discussion

The aim of this pilot randomised trial is to compare the feasibility and preliminary effectiveness of an economic incentive package (cash + motivational SMS) versus a control for improving caregiver wellbeing. package. The results from this pilot trial will provide the critical data to determine whether a larger-scale RCT is warranted and feasible. This intervention represents an integrated approach, specifically designed to target aspects that matter to caregiver’s wellbeing in this setting (such as financial problems, mental health, relational problems, support, physical health) [14]. It is designed to be delivered remotely by lay counsellors and thus allows access to care for a vulnerable group who otherwise may not be able to receive such care due to time, transport limitations, lack of state psycho-social support services, along with the national social limitations implemented due to the COVID-19 pandemic.

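### The primary outcome is defined inconsistently and does not match the feasibility aim and progression rule, while wellbeing is still powered and tested as a primary efficacy contrast

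*Protocol article*

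**What the plan says.** All references are to the protocol article.

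- **Aim.** The Background states: "The overall aim of this pilot randomised control trial (RCT) is to evaluate the feasibility of a future large scale randomised controlled trial". The Abstract's background paragraph and the Discussion are wider; the Discussion says the trial will "compare the feasibility and preliminary effectiveness of an economic incentive package".
- **One primary outcome.** The Abstract (Methods) says "The primary outcome measure, caregiver wellbeing, will be measured using the CarerQoL instrument". The Sample size section says "Our primary outcome is pre-post between difference in caregiver wellbeing scores".
- **Three primary outcomes.** Under the heading "Primary clinical outcome measures informing our sample size" the article lists the change in wellbeing, a consent rate of at least 80% and a retention rate of at least 80%.
- **Primary objectives.** There are seven. The wellbeing difference comes first; the others concern feasibility, procedures and acceptability.
- **Decision rule.** The Progression criteria begin "The following criteria must be met in order to consider progression to a main RCT" and list only retention and enrolment of eligible participants, each at 80% or more.
- **Efficacy machinery.** The Sample size section starts from wellbeing. The Statistical analysis section compares the wellbeing change between arms by linear regression. Limitations, item 7, says the sample gave 80% power for treatment effects.
- **Masking.** The Blinding section says "This is an open label trial as field staff will be involved in the intervention delivery and study assessments".

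**The concern.** A reader cannot tell from the article whether the trial has one primary outcome or three. Nor does the outcome named alone as primary match the rule that decides whether a main trial follows. That leaves room to report the pilot as positive or negative on wellbeing when its stated question is whether eligible caregivers enrol and stay.

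The wellbeing contrast is also a fragile basis for a primary claim. The caregiver rates her or his own wellbeing to an interviewer, knows the allocation, and receives cash in one arm only. Field staff both deliver the intervention and take part in the assessments. A larger sample does not remove bias from these sources. If the power statement is also less secure than it reads, neither a significant nor a null wellbeing result carries the weight that a primary outcome implies.

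**Working it through.** **1. The definitions side by side**

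| Place | Feasibility | Wellbeing |
|---|---|---|
| Background, overall aim | yes | only as the question of the future trial |
| Abstract (background) and Discussion, aim | yes | yes, as preliminary effectiveness |
| Abstract (Methods), primary outcome | no | yes, alone |
| Sample size, primary outcome | no; described as also served by N = 100 | yes, alone |
| Primary outcome measures section | consent and retention | yes |
| Primary objectives | several of seven | first of seven |
| Progression criteria | consent and retention | no |

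The two statements of a single primary outcome conflict with the list of three, and neither agrees with the progression rule.

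**2. The plan's own sample size**

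Inputs from the Sample size section: "Assuming a mean caregiver wellbeing VAS score of 6.5 in M1 versus 8.5 in M5 (SD1.9) in the intervention arm", 80% power, stated effect δ = 0.6 to 0.5, 15 per arm. Alpha is not given; two-sided 5% is assumed.

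n per arm = 2 × (1.96 + 0.8416)² × (SD / difference)²

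- Difference 2.0, SD 1.9 (2.0/1.9 = 1.05 SD): 2 × 7.849 × 0.9025 = 14.2, so 15. The stated figure is reproduced (t-test version 15.2, so 16).
- δ = 0.5: 2 × 7.849 / 0.25 = 62.8, so 63 (t test 64).
- δ = 0.6: 2 × 7.849 / 0.36 = 43.6, so 44 (t test 45).

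The 15 per arm therefore belongs to 1.05 SD and not to the δ in the same sentence. The 2.0 points are also the intervention arm's own change from M1 to M5; using them as a between-arm effect assumes no change in controls.

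**3. Power at the planned size**

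The section allows for 20 refusals or losses out of 100. Split evenly, that leaves 40 per arm; with none it is 50. Two-sample t test, non-centrality δ × √(n/2), df = 2n − 2:

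| Effect | 40 per arm | 50 per arm |
|---|---|---|
| 0.5 SD | 59.8% | 69.7% |
| 0.6 SD | 75.5% | 84.4% |
| 1.05 SD | above 99% | above 99% |

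The normal approximation gives 61% and 71% at 0.5 SD, and 77% and 85% at 0.6 SD.

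**4. Precision of the wellbeing estimate**

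95% half-width = t × √(2/n):

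- 40 per arm: 0.445 SD, and 0.445 × 1.9 = 0.85 points.
- 50 per arm: 0.397 SD, and 0.397 × 1.9 = 0.75 points.

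This takes 1.9 as the SD of the quantity analysed. For a change score the SD is 1.9 × √(2(1 − r)), which equals 1.9 only if the baseline–endline correlation r is 0.5. The article does not give r.

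**5. Precision if retention leads**

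An observed 80 of 100 retained has a 95% Wilson interval of 71% to 87%.

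**The case against.** A pilot may properly list an effect estimate among its primary objectives and still base the go/no-go decision on feasibility. Keeping wellbeing out of the progression rule protects that decision from a chance efficacy result. The first primary objective is to estimate a difference, the planned regression yields an estimate, and no significance rule for declaring effectiveness is stated. The Limitations concede possible bias from the lack of blinding. All of this stands. It does not settle whether there is one primary outcome or three, and the Sample size section and the Limitations do use the language of powered detection.

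Three stronger readings are tempting and go too far:

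- *Wellbeing is the only primary outcome in the document.* This is true of the Abstract and the Sample size section, but the outcome-measures section and the primary objectives include feasibility. The wider aim in the Abstract and Discussion also gives wellbeing a role.
- *The trial cannot support any efficacy test, because significant results would be grossly exaggerated.* If the true effect were 0.2 to 0.3 SD, a significant estimate would overstate it about 1.7 to 2.8 times. Those effects appear nowhere in the article. At its own 0.5 to 0.6 SD the overstatement is about 1.1 to 1.3 times, and at 1.05 SD there is none.
- *The published headline will be efficacy.* That is a prediction; the article does not say so.

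It is also fair to object that demoting a named primary outcome after follow-up has its own credibility cost. This bears on how the fix is made.

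**Conclusion.** The point holds as an inconsistency in the definition of the primary outcome and a mismatch with the decision rule. The aim in the Background and the whole of the progression rule concern feasibility, while the Abstract and the Sample size section name wellbeing alone and the analysis treats it as a powered between-arm contrast.

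The 80% power claim is not secure. Over δ = 0.5 to 0.6, power is about 60% to 76% at 40 per arm and 70% to 84% at 50. It is ample only if the true between-arm difference is the full 2.0 points. These figures assume a two-sided 5% test, equal SDs, and losses split evenly between arms. The conflict between the passages depends on none of these assumptions. Bias from open-label, self-reported assessment is a separate reason for caution, and its size cannot be computed from the article. The change is a cheap improvement and worth making.

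**What to change.** In the Abstract (Methods), Primary objectives, Primary clinical outcome measures and Sample size sections, name consent and retention, as defined in the Progression criteria, as the primary outcomes. Report the between-arm wellbeing difference as a preliminary estimate with its 95% confidence interval, and make no claim of effectiveness based on significance. Bring the 80% power statement in the Limitations into line, either by tying it to the effect size it rests on or by removing it.

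No new data and no change of sample size are needed. There are two costs. The paper loses a primary efficacy claim. And since the Trial status section says that enrolment, delivery and follow-up are complete and analysis is underway, the change is a late one: it should be dated, disclosed as a clarification made at that stage, and accompanied by the full wellbeing result so that it cannot look like selective reporting.

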**Discussion:**

This study will provide scientific direction for the design of a larger randomised controlled trial exploring the effects of an economic incentive for improving caregiver wellbeing. The feasibility of conducting study activities and delivering the intervention remotely in the context of a pandemic will also be provided.

**Trial registration:**

PACTR202203585402090. Registry name: Pan African Clinical Trials Registry (PACTR); URL: https://pactr.samrc.ac.za/; Registration. date: 24 March 2022 (retrospectively registered); Date first participant enrolled: 03 November 2021

**Supplementary Information:**

The online version contains supplementary material available at 10.1186/s40814-023-01237-x.

## Background

Improving caregiver wellbeing in the post-COVID-19 context has become a public health priority. The pandemic has interrupted progress towards a key policy goal for carers and especially older persons (SDG 3: improving health and wellbeing for all ages) [1]. The mental and financial strain linked to this unpaid role is linked to negative health outcomes [2, 3] and economic consequences such as potential reduction in human capital accumulation and productivity losses [4]. Sub-Saharan Africa (SSA), with an estimated 1.54 million adolescents living with HIV (ALHIV), constitutes 88% of the global population of the ALHIV [5]. Despite remarkable progress in the scale-up of antiretroviral therapy (ART) in SSA, several studies report poor ART adherence, virological non-suppression [6] and high levels of depressive symptoms among this population [7]. A major predictor of favourable HIV and mental health outcomes among ALHIV is quality caregiving, which entails ensuring that the basic needs of adolescents are met (e.g. shelter, adequate nutrition, education) and providing emotional support through key milestones as they transition from childhood to adolescence (i.e. disclosure, self-acceptance and belonging, pubertal development, coping, relationship building) [8, 9]. However, caregivers are hampered in their ability to provide adequate support to ALHIV because of the barriers they encounter in maintaining wellbeing which are influenced by determinants that extend beyond the individual [10] such as gender inequalities and norms, stigma, lack of family or social support [11], household, socio-economic status [12, 13], geographic constraints in accessing health and social services [14]. The COVID-19 pandemic has further amplified these social determinants of wellbeing [15, 16]. Understanding which interventions are effective and feasible for improving caregiver wellbeing is an important first step for assessing how best to improve the quality of life among carers and ALHIV.

Most caregivers in SSA are older persons or females who are outside of the labour market and residing in skipped generation households that are at high risk of becoming impoverished [17, 18]. The gendered caregiving role intersects with poverty and other demographic, cultural and socio-political factors, (old age, diet, roles in in the household, education, access to basic health and social services, stigma) [19, 20]. Older carers from lower socio-economic status, living in rural areas with poor access to health and social services, and those that are HIV affected are likely to experience more stigma, severe mental health issues and hence, lower levels of wellbeing [21]. Evidence from SSA shows that caregivers’ fears around the consequences of inadvertent disclosure of adolescents’ HIV-positive status as well as their own, financial hardships, multiple caregiving responsibilities; and the lack of social support services are associated with pronounced negative effects on their mental health status (e.g. anxiety levels and depressive symptoms) and overall wellbeing (social isolation, purpose in life) [22–24]. The challenges with caregiving were further exacerbated by the COVID-19 pandemic, with caregivers experiencing adverse health, psychosocial and financial outcomes due to increased duties and caregiver burden [25] arising from disruptions of normal external support services [26]. It has also been reported that family caregivers demonstrated poorer mental health and physical health during the pandemic compared to non-caregivers [27].

In addition to tending to the special needs of ALHIV (e.g. adherence, clinic visits, transport costs, nutrition) [28, 29], primary caregivers are also challenged with looking after the basic needs of entire households [29–31]. Elderly caregivers, for instance, often stretch state pension grants to meet these needs [31]. Oftentimes caregivers have to resort to borrowing or selling essential resources to cope with their economic burden [29]. These households are thus economically vulnerable and the children living in them have the heightened risk of being malnourished [30].

Key barriers to caregiver wellbeing include lack of financial resources to support and care for ALHIV, attending to their personal care needs and household responsibilities, as well as fear of stigma [31]. Previous studies have shown that caregiver wellbeing in this setting is grounded in one’s ability to fulfil role-relationships [32, 33]. Several trials have shown that financial incentives are effective in improving HIV testing, including adherence to treatment and clinic appointments [34, 35]. Furthermore, financial incentives have been linked to improvements in quality of life [36]. Individuals are generally present-biased, loss-averse and ascribe high weights to low probability events [37]. Financial incentives may overcome these biases by offsetting the immediate opportunity costs linked to health-behaviour change along with uncertain and delayed gains [38]. Cash incentives for caregivers could potentially improve their quality of life by providing the resources to meet their personal care needs and the fiscal resources needed for them to plan and meet their caregiver and household responsibilities [31, 39]. More importantly, they could serve as recognition for the indispensable care they provide, thereby intensifying their sense of responsibility and quality of care provided to ALHIV.

Nudges are a key behavioural economics strategy (“nudge”) for health-related behaviour change [40, 41]. Nudges seek to influence decision-making by specifically targeting behavioural barriers. Nudges have been successfully used to develop low-cost solutions targeting key behavioural barriers and social norms impacting health outcomes [42]. Whilst there are mixed results on the effectiveness of nudges in certain settings, nudges have shown positive results in areas such as mental health [43, 44], HIV [45–47] and dietary choices [48]. In SSA, short-text messaging service (SMS) technology has been used in nudge approaches to deliver health information, motivate individuals to access care and adhere to treatment [47]. These studies also suggest that nudges can be readily brought to scale in these settings. Evidence from SSA indicates that SMS reminders sent to caregivers have been effective in promoting appointment attendance and medical adherence [47]. Key debates regarding the nudge approach revolve around its inability to solve complex health problems given its focus on targeting specific behavioural barriers when it comes to uptake, adherence and access to health interventions [49], the lack of causal evidence and lack of understanding of patterns [50, 51]. Ethical concerns noted about nudging are that it diminishes one’s autonomy and agency [51]. To our knowledge, no study has re-designed and evaluated these economic incentives, cash and SMS reminders, for the promotion of quality of life among caregivers of ALHIV.

Pilot and feasibility studies are an important first step in adapting and testing complex interventions in public health [52]. Pilot studies facilitate in-depth understanding of the conduct and applicability of an intervention which can enhance the design and conduct when evaluated at scale [53]. The overall aim of this pilot randomised control trial (RCT) is to evaluate the feasibility of a future large scale randomised controlled trial in examining the effectiveness of an economic incentive package (cash + SMS) in improving wellbeing among caregivers of ALHIV.

